### Participant timeline

The participant timeline is summarized in Table 3. Candidates who agree to participate are checked for eligibility based on the inclusion/exclusion criteria, and enrolment is completed after confirmation of eligibility. Physical examination, Eastern Cooperative Oncology Group performance status (PS), body weight, body height, complete blood count (CBC), serum biochemistry, urine analyses, creatinine clearance, chest X-ray and percutaneous saturation of oxygen (SpO_2_) are performed within 14 days before registration. Electrocardiography, computed tomography (CT) of the chest, magnetic resonance imaging (MRI) of the primary site and additional CT/MRI of the associated lymph nodes area are performed within 35 days before registration. Tests of hepatitis and 18-fluorodeoxyglucose positron emission tomography–computed tomography (PET-CT) or bone scintigraphy should also be performed before registration. Participants should commence the treatment protocol within 7 days (arm A) or 28 days (arm B) of registration.

**Table 3 TB3:** The study schedule

Arm A	Enrolment	NAC			Surgery		AC		Follow-up
		1	2	3	Before	After	1	2	
Informed consent	○	◯							
Inclusion/exclusion criteria	◯								
Physical examination	○	○	○	○	○	○	○	○	○
Body weight	○	○	○	○	○		○	○	
Height	○								
PS	○	○	○	○	○		○	○	
Blood examinations^a^	○	○	○	○	○		○	○	○
Urine analysis	○		○	○			○	○	
Creatinine clearance	○								
HBs-Ag, HBc-Ab, HBs-Ab, HCV-Ab	○								
Chest X-ray	○		○	○	○		○	○	○
Chest CT	○				○				○
MRI of primary site	○				○				○
CT/MRI for lymph nodes	○								
PET-CT/Bone scintigraphy	○								
SpO_2_	○		○	○			○	○	
ECG	○				○				
Adverse events		○	○	○	○	○	○	○	○
Arm B	Enrolment	Surgery		AC			Follow-up		
		Before	After	1	2	3			
Informed consent	○								
Inclusion/exclusion criteria	◯								
Physical examination	○		○	○	○	○	○		
Body weight	○								
Height	○								
PS	○			○	○	○			
Blood examinations^a^	○	○		○	○	○	○		
Urine analysis	○			○	○	○			
Creatinine clearance	○								
HBs-Ag, HBc-Ab, HBs-Ab, HBC-Ab	○								
Chest X-ray	○			○	○	○	○		
Chest CT	○						○		
MRI of primary site	○						○		
CT/MRI for lymph nodes	○								
PET-CT/Bone scintigraphy	○								
SpO_2_	○			○	○	○			
ECG	○								
Adverse events			○	○	○	○	○		

^a^CBC, serum biochemistry. PS, Performance Status; SpO_2_, percutaneous oxygen saturation; ECG, electrocardiogram.

The criteria for dose reduction or discontinuation are set as follows. In the event of severe myelosuppression, liver dysfunction, diarrhoea, oral mucositis or infection, the dose is reduced by 20% per step in the next course. Further chemotherapy should be terminated if the dose reduction criteria are still met after two steps of dose reduction.

In the event of severe pneumonitis, increased creatinine, arrhythmia, cardiac dysfunction, vertigo, nervous system disorder or haematuria, the chemotherapy should also be discontinued. No other anti-cancer drugs, hormone therapies other than steroids, radiotherapy or immunotherapy should be used during protocol treatment.

In arm A, if any of the following (i–iv) are met after the start of NAC, subsequent chemotherapy should be discontinued: (i) exacerbation of disease after the start of protocol treatment; (ii) the protocol treatment cannot be continued due to adverse events including Grade 4 non-hematologic toxicity and delay of >14 days of the start of the following course; (iii) the patient requests termination of protocol treatment for reasons related to adverse events; and (iv) the patient requests termination of protocol treatment for reasons unrelated to adverse events. In case of discontinuation of NAC, protocol treatment is continued, and surgery is performed after determining tumour reduction efficacy as far as possible. However, AC is not given, and protocol treatment is discontinued upon completion of surgical treatment. Protocol treatment should be discontinued if any of the following (i–vi) are met: (i) progression of disease; (ii) the protocol treatment cannot be continued due to adverse events including Grade 4 non-hematologic toxicity; (iii) the patient requests termination of protocol treatment for reasons related to adverse events; (iv) the patient requests termination of protocol treatment for reasons unrelated to adverse events; (v) death during protocol treatment; and (vi) post-enrolment exacerbation prior to the initiation of protocol treatment (inability to start the protocol treatment due to rapid progression), the discovery of protocol violation, change of treatment due to a change in the pathological diagnosis after enrolment, or other reasons that make the patient ineligible for protocol treatment.

### Sample size

Based on the background provided, the 3-year OS for arms A and B are assumed to be 85%. The non-inferiority margin is 8% in 3-year OS (acceptable HR of 1.61). Assuming 6 years of accrual, 3 years of follow-up, α = 10% (one-sided) and a non-inferiority margin of 1.61, the planned sample size is set at 224 in total and 112 in each arm based on the Schoenfeld & Richter’s method (18). If enrolment is better than expected, the power would be changed from 70% to 75% or 80%.

### Data collection, management, monitoring and auditing

The investigator uses the electronic data capture (EDC) system of the JCOG web entry system to input data into the case report form. Any adverse events are closely monitored by the investigator. Investigators should report severe adverse events to the institutional investigator and study coordinator/study chair and then to the CRB of the National Cancer Center Hospital, as appropriate. The EDC system, Electronic Document Management System (E-DMS) Online (EPS Corporation, Tokyo, Japan), is used for clinical data entry, data management and central monitoring.

Two interim analyses are conducted during the trial to determine whether the primary aim has been achieved: the first interim analysis is conducted during accrual to decide whether or not it is reasonable to continue accrual; the second interim analysis is conducted early after the end of accrual to determine whether to continue follow-up for the planned period. In both cases, if it is determined that the primary aim has been achieved, the study is terminated, and the results of the study are promptly published. In-house monitoring is performed every 6 months by the JCOG Data Center to evaluate the study progress and improve the data quality.

### Statistical analysis

All statistical analyses will be conducted at the JCOG Data Center. The primary analysis will be performed using the stratified Cox proportional hazards model with stratified allocation adjustment factors excluding the centre: histological grade (Grade 2 vs. Grade 3) and T-classification (T2 vs. T3–4). The confidence intervals are constructed with the Wald method. The non-inferiority is confirmed when the upper limit of confidence interval of the HR adjusted for multiplicity is below the margin of 1.61.

To examine the interaction between the treatment effect and the background factors, subgroup analyses will be conducted in the following factors: age, PS, sex, primary site, pathological grading, histological type, tumour size, surgical procedure, surgical margin, post-operative radiation and completion of protocol treatment. Since these analyses are not performed with sufficient power and are not adjusted for multiplicity, results are only to be interpreted as exploratory.

## Discussions

Surgery is the most important treatment for STSs. Chemotherapy has been reported to have an additive effect on OS in high-risk patients and is listed as a consideration in the respective guidelines (16,17). The unsolved current clinical issue is the lack of evidence regarding whether surgery, the most important therapeutic intervention, should be performed first or after chemotherapy for resectable high-risk STS.

If the study has a positive result, the standard treatment for resectable high-risk STSs changes to immediate surgery followed by three courses of AC. It reduces the incidence of extended surgery and amputation of affected limbs and shortens the duration of treatment.

If the result is negative, the standard treatment in Japan remains three courses of NAC followed by surgery and two courses of AC. The result indicates that three courses of AC are inferior to five courses of perioperative chemotherapy. Taken together with the previous report showing that three courses of NAC were non-inferior to five courses of perioperative chemotherapy (8), these are the first results to suggest that the OS benefit of chemotherapy in the neo-adjuvant setting may be greater than in the adjuvant setting for STS.

Whether the results of this trial are positive or negative, they will indicate whether resection or chemotherapy should be performed first.

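### A negative result would show only that non-inferiority was not confirmed, not that three courses of adjuvant chemotherapy are inferior as the Discussions section states

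*Protocol article*

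**What the plan says.** Statistical analysis gives one criterion for the primary endpoint: "The non-inferiority is confirmed when the upper limit of confidence interval of the HR adjusted for multiplicity is below the margin of 1.61". The article states no criterion for concluding inferiority and describes no inconclusive outcome.

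Sample size assumes 3-year overall survival of 85% in both arms, a one-sided α of 10%, 6 years of accrual, 3 years of follow-up and 224 patients. It puts power at 70%, to be raised to 75% or 80% only if enrolment goes better than expected.

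Discussions then describes each possible result. After a negative one, the Japanese standard (three neoadjuvant courses, surgery, two adjuvant courses) stays in place. The next sentence reads: "The result indicates that three courses of AC are inferior to five courses of perioperative chemotherapy". Two further statements follow:

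- Together with the European trial in which three neoadjuvant courses were non-inferior to five perioperative courses, a negative result would suggest that the survival benefit of chemotherapy may be greater before surgery than after it.
- Either result will show whether resection or chemotherapy should come first.

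**The concern.** The null hypothesis of the primary test is that the HR is at least 1.61. Failing to reject it leaves open every value inside the confidence interval, and that interval may include 1 or values below 1. Reading the failure as a finding of inferiority takes absence of confirmation for evidence of the opposite.

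The comparison with the European trial needs three adjuvant courses to have been shown worse than five perioperative courses, so it inherits the error. The closing sentence does too, because an inconclusive trial does not settle the order of treatment. The article presents the trial as the first randomized comparison of its kind and says there is no evidence worldwide on which treatment should come first. A negative result would therefore be read closely, and the reading announced in advance should be one that the test can support.

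**Working it through.** **Inputs (Sample size).** 3-year survival 85% in both arms, so true HR = 1.0; margin HR 1.61; one-sided α = 10%; 6 years of accrual plus 3 of follow-up; N = 224, 1:1; power 70%.

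**Assumptions not in the article.** Exponential survival, uniform accrual, no losses unless stated, and an unadjusted two-sided 80% interval to match the one-sided 10% level.

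**1. The plan's own figures.**
- Margin: ln(0.77)/ln(0.85) = 1.608, which agrees with 1.61.
- Deaths needed at 70% power (Schoenfeld): 4 × (1.2816 + 0.5244)² / (ln 1.61)² = 57.5, rounded up to 58. The Freedman formula gives 60.
- Hazard: λ = −ln(0.85)/3 = 0.0542 per year.
- Probability of death by the analysis: 1 − (e^(−3λ) − e^(−9λ))/(6λ) = 1 − (0.850 − 0.614)/0.325 = 0.274.
- N: 58/0.274 = 212 (Schoenfeld) or 60/0.274 = 219 (Freedman). Schoenfeld with an assumed 5% loss gives 212/0.95 = 223.

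The stated 224 is therefore reproduced closely, and the sample size is not in question.

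**2. Where non-inferiority fails.** With 224 patients and no losses, expected deaths are 224 × 0.274 = 61.4, and SE(ln HR) = 2/√61.4 = 0.255. The upper limit is below 1.61 only if the observed HR is below 1.61 × exp(−1.2816 × 0.255) = 1.16. At that boundary the 80% interval runs from 0.84 to 1.61 and includes 1.

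**3. Where inferiority would begin to show.** The lower 80% limit exceeds 1 only if the observed HR is above exp(1.2816 × 0.255) = 1.39. A 95% interval needs about 1.65.

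**4. How often the trial is negative.** P(negative) = 1 − Φ[(ln 1.16 − ln HR)/SE].

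| Quantity | 61.4 deaths | 58 deaths |
|---|---|---|
| Non-inferiority fails above observed HR | 1.16 | 1.15 |
| Lower 80% limit exceeds 1 above observed HR | 1.39 | 1.40 |
| P(negative), true HR 0.90 | 16% | 17.5% |
| P(negative), true HR 1.00 | 28% | 30% |
| P(negative), true HR 1.10 | 42% | 43% |

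(For 58 deaths, SE = 0.263 and the threshold in the formula is 1.15.) If power is raised to 75% or 80%, the figure at HR 1.00 falls to 25% or 20% by definition.

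**5. What those negative trials would show.** With equal arms, the lower 80% limit exceeds 1 in 10% of all trials. Among the negative ones, 1 − 0.10/0.279 = 64% would have an 80% interval that includes 1 (66% with 58 deaths).

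**The case against.** Several points on the other side stand.

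- The sentence is interpretive text. The decision rule itself is correctly worded, and endpoint, model and sample size are untouched.
- Keeping the current standard after a negative result is the right consequence of a failed non-inferiority test. Between observed HRs of 1.16 and 1.39 the treatment decision would be the same under either wording.
- The Introduction reports the group's previous non-inferiority trial properly: non-inferiority was not shown, so the standard was kept. The comparator there is not called inferior.
- The thresholds above ignore the multiplicity adjustment for two interim analyses, which could move them slightly.

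A reader might also infer more than the document supports:

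- **That the plan treats a negative result as proof, or would report that immediate surgery costs lives.** The article says the result indicates inferiority, and it hedges the neoadjuvant inference. It makes no claim of proof and none about lives lost.
- **That the inferiority conclusion would be false in a large share of negative trials.** The calculation gives the chance of a negative result when the arms are equal. The share of negative trials in which the arms are equal would need a prior distribution for the HR, which the document does not give.

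None of this rescues the sentence. To say a result indicates inferiority is a directional conclusion, and the stated rule cannot deliver one. An analysis plan that handled this correctly would contradict the article, so the objection is to what is written and not to missing detail.

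**Conclusion.** Wrong as written, in interpretation only. Under the stated rule, a negative result means that an HR of 1.61 was not excluded. With truly equal arms that happens in about 28–30% of trials at the planned 70% power. With about 61 deaths, observed HRs of about 1.16 to 1.39 would be labelled inferior although the two-sided 80% interval still includes 1.

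These figures rest on the working assumptions given above. The logical point does not depend on them: at any power below 100%, some negative results will not show inferiority.

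**What to change.** In Discussions, replace the inferiority sentence with a statement that non-inferiority was not confirmed and the current standard is therefore retained. This follows the wording the Introduction already uses for the group's previous trial.

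Add that inferiority will be stated only if the confidence interval for the HR, at a level fixed in advance, lies wholly above 1, and that the result is otherwise inconclusive. The choice of level is the sponsor's; a formal second test at the 80% level is not required.

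Make two later statements conditional on inferiority having been shown in that sense: that neoadjuvant benefit may exceed adjuvant benefit, and, for a negative result, that the trial will indicate which treatment comes first.

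The cost is wording only, with no extra patients or data. The retained standard, sample size and primary test stay as they are. The price is that a negative trial will support a weaker statement than the article now announces.

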Toxicity with AI treatment is also a concern. The most common adverse events are hematologic toxicity, with grade 3/4 leucopoenia and neutropenia almost inevitable, and grade 3/4 non-hematologic toxicity with nausea and anorexia is also common. Given the severe toxicity, a randomized controlled trial (RCT) of three courses of NAC followed by surgery and two courses of AC versus three courses of NAC followed by surgery was recently conducted in Europe (8). The results showed that the 5-year OS was 71% (95% CI: 63–77%) in the former arm compared with 68% (95% CI: 60–75%) in the latter arm, with a hazard ratio (HR) of 1.00 (90% CI: 0.72–1.39), proving non-inferiority in OS. Regarding toxicity, renal dysfunction occurred in 1.5% of patients receiving five courses of chemotherapy but not in those receiving three courses. The incidence of hematologic toxicity also increased with two additional courses, again suggesting that an increase in the number of courses is associated with an increase in toxicity. However, the rationale for using three courses of NAC as the test treatment was not stated in that paper. Globally, there is no evidence of whether chemotherapy or surgery should be performed first. Surgery after NAC is the standard treatment in some countries including Japan and Italy, but other countries and physicians consider resection as the first treatment, with chemotherapy as an option or post-operative consideration. Indeed, in a recently reported clinical trial in Germany for STS, resection was followed by chemotherapy (15).

The National Comprehensive Cancer Network (NCCN) guidelines make no recommendations regarding optimal resection timing or number of courses since there is no evidence (16). The ESMO Clinical Practice Guidelines state that perioperative adjuvant chemotherapy for STSs is a treatment option for high-risk patients. They also mention that three courses of NAC with AI may be effective but do not address the superiority of NAC over AC (17).

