The current clinical challenge in this field is to optimize the balance between the survival benefit of perioperative chemotherapy with AI and the toxicity and risk of extended surgery. From this viewpoint, the immediate surgery followed by three courses of AC is expected to be an effective and safer treatment since it will avoid the risk of extended resection due to tumour growth during NAC and reduce the number of chemotherapy courses. We, therefore, designed a randomized phase III trial of Neo-adjuvant and adjuvant chemotherapy vs. Adjuvant Chemotherapy for LocalizEd Soft tissue Sarcoma (NACLESS trial) to confirm the non-inferiority of three courses of AC with AI compared with three courses of NAC and two courses of AC with AI for localized high-risk STS patients for establishing a better standard treatment.

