### Interventions

Patients will be randomized to arm A or B (Fig. 1) at the JCOG Data Center. Arm A will receive standard treatment (three courses of NAC, surgery and two of AC) and arm B will receive trial treatment (surgery and three courses of AC), with AI comprising adriamycin (30 mg/m^2^, days 1, 2) and ifosfamide (2 g/m^2^, days 1–5).

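### The arms differ in both sequence and number of courses, so neither result can by itself settle whether surgery or chemotherapy should come first, and a failed non-inferiority test does not show inferiority

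*Protocol article*

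**What the plan says.** Interventions defines the control arm first: "Arm A will receive standard treatment (three courses of NAC, surgery and two of AC"). The test arm is described next, in the same sentence, where the article states that "arm B will receive trial treatment (surgery and three courses of AC"). The Introduction makes clear that both changes in arm B are intended: "it will avoid the risk of extended resection due to tumour growth during NAC and reduce the number of chemotherapy courses".

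Discussions then draws three conclusions that go beyond the comparison of the two strategies:

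- For a negative result: "The result indicates that three courses of AC are inferior to five courses of perioperative chemotherapy".
- Still for a negative result, with the European trial of three against five courses as a bridge ("Taken together with the previous report showing that three courses of NAC were non-inferior to five courses of perioperative chemotherapy (8")), it says that the findings would suggest that "the OS benefit of chemotherapy in the neo-adjuvant setting may be greater than in the adjuvant setting for STS".
- For either result: "Whether the results of this trial are positive or negative, they will indicate whether resection or chemotherapy should be performed first".

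The Introduction reports the European trial "with a hazard ratio (HR) of 1.00 (90% CI: 0.72–1.39), proving non-inferiority in OS".

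**The concern.** A two-arm trial whose arms differ in two components estimates the effect of changing both. Nothing inside this trial separates the effect of operating first from the effect of giving two fewer courses. The closing sentence nevertheless promises an answer on order alone, whichever way the trial ends. For a positive result the article offers no argument that isolates order. For a negative result it first turns a failed non-inferiority test into a finding of inferiority, and then leans on an external trial to set course number aside.

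Discussions names the order of surgery and chemotherapy as the unsolved clinical issue, so readers will look to this sentence for the answer. A negative result could be reported as evidence for chemotherapy first when it reflects two fewer courses, or chance.

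**Working it through.** **Inputs.** Per-course doses: adriamycin 30 mg/m² on 2 days, ifosfamide 2 g/m² on 5 days (Interventions). 3-year OS 85% in both arms, margin 8 points or HR 1.61, 6 years of accrual, 3 years of follow-up, one-sided alpha 10%, 224 patients, power 70% (Sample size). European trial: HR 1.00, 90% CI 0.72 to 1.39 (Introduction).

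**1. What differs between the arms.**
- Adriamycin: 30 × 2 = 60 mg/m² per course; × 5 = 300, × 3 = 180.
- Ifosfamide: 2 × 5 = 10 g/m² per course; × 5 = 50, × 3 = 30.
- Both totals fall by 40%, while the order of surgery and chemotherapy is also reversed.

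**2. The plan's own figures.**
- Margin: ln 0.77 / ln 0.85 = 1.608, which matches 1.61.
- Events needed: 4(1.282 + 0.524)² / (ln 1.61)² = 57.5, so 58 (Schoenfeld); Freedman's formula gives 60.
- Event probability: the hazard is −ln 0.85 / 3 = 0.0542 per year. With exponential survival and uniform accrual, the probability is 1 − (e^(−3 × 0.0542) − e^(−9 × 0.0542)) / (6 × 0.0542) = 0.274.
- Patients: 58 / 0.2743 = 212, or 60 / 0.2743 = 219. The stated 224 is reproduced closely; an assumed 5% allowance for losses would give 212 / 0.95 = 223.
- Expected deaths at 224 patients without losses: 224 × 0.2743 = 61.4. Power is then about 72%, in line with the stated 70%.

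**3. When non-inferiority fails.** SE of log HR ≈ 2/√61.4 = 0.255. The upper limit falls below 1.61 only if the observed HR is below exp(0.476 − 1.282 × 0.255) = 1.16. The article adjusts the confidence interval for multiplicity over two interim analyses, so the real threshold is no higher than this. At 70% power, 30% of trials fail when the true HR is 1.00 (28% at the computed 72%).

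**4. What course number could explain.** Assume that the two effects multiply and that the European interval transfers. Then sequence HR = trial HR / course-number HR. The European interval is symmetric on the log scale, so the direction of its HR does not matter.

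| Observed trial HR | Implied sequence HR, course HR from 0.72 to 1.39 |
|---|---|
| 1.00 | 0.72 to 1.39 |
| 1.16 | 0.83 to 1.61 |
| 1.39 | 1.00 to 1.93 |
| 1.61 | 1.16 to 2.24 |

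For a failed trial with an observed HR between about 1.16 and 1.39, the range includes 1, so course number could account for the whole estimate. A course HR of 1.39 uses ln 1.39 / ln 1.61 = 0.329/0.476 = 69% of the log margin. If it were the truth and order had no effect, this trial would declare non-inferiority only about 25% of the time.

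**5. Adding this trial's own error.** The European SE is ln(1.39/0.72) / (2 × 1.645) = 0.200. Combined: √(0.255² + 0.200²) = 0.324. The 90% limits multiply or divide the estimate by exp(1.645 × 0.324) = 1.70:
- observed 1.00: 0.59 to 1.70
- observed 1.16: 0.68 to 1.98
- observed 1.61: 0.94 to 2.74

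**The case against.** The strongest reply is that the plan already compares packages. The aim, the margin and the primary analysis all concern the two whole strategies, and so do the two practice conclusions in Discussions, where the standard either changes to surgery plus three courses or stays as it is. The closing sentence can then be read as saying which strategy, and so which first step, to adopt. All of this stands for the design. It does not rescue the closing sentence, which speaks of order alone and of both outcomes.

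Three stronger readings are tempting, and the documents do not support them:

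- *That the article treats the European result as proof of no difference and asserts a larger neo-adjuvant benefit.* It does not. It says non-inferior, and the neo-adjuvant sentence is worded as a suggestion and names its source. Its logic is an indirect comparison through the shared five-course strategy, which sets three adjuvant against three neo-adjuvant courses and so holds course number at three. What it lacks is an interval and a note that the European trial used epirubicin (Table 1) and gave neo-adjuvant chemotherapy in both arms.
- *That any negative result could be due entirely to fewer courses.* At an observed HR of 1.61, the range that ignores this trial's error is 1.16 to 2.24 and excludes 1. The point holds near the failure threshold. At 1.61 it rests on sampling error, with a lower limit of 0.94.
- *That a positive result says nothing about order.* If two fewer courses cannot improve survival, the sequence HR cannot exceed the trial HR, so a trial HR shown to be below 1.61 bounds the sequence HR below 1.61 as well. This is partial information under an assumption that the article does not state. It is weaker than an answer to which should come first.

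**Conclusion.** The closing sentence of Discussions, and the sentence equating a negative result with inferiority, are wrong as written. The hazard ratio identifies only the joint effect of changing the order and removing two courses. A failed test requires no more than an observed HR above about 1.16, and has a probability of about 30% when the arms are identical. It therefore does not show inferiority, and near that threshold it cannot be credited to order rather than course number.

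The figures assume exponential survival, uniform accrual, no losses, no interim adjustment, effects that multiply on the hazard-ratio scale, and a European interval that carries over to a different regimen. The central point, that one contrast cannot separate two components, needs none of these. It concerns interpretation only: the aim, margin, sample size and primary analysis remain valid for the package comparison, and a positive result could support adopting arm B as a whole.

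**What to change.** In Discussions, and in any later report:

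1. Replace the closing sentence with a conclusion about the two strategies as packages: surgery then three courses, against three courses, surgery and two courses.
2. State that sequence and number of courses cannot be separated in this trial.
3. Describe a negative result as non-inferiority not shown, in place of the statement that three adjuvant courses are inferior.
4. Keep the hedged neo-adjuvant versus adjuvant statement only as an exploratory cross-trial indirect comparison. Give its interval with both trials' errors propagated, and state the epirubicin regimen difference.

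The cost is wording. Treatment, allocation, endpoint, margin, sample size and analysis do not change. The trial gives up a claim about order that its design cannot support.
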